# 2 Background

With development and improvement of assisted reproductive technology, good quality embryos in most of patients can be frozen in vitro fertilization cycle. Frozen-thawed embryo transfer (FET) is an important technology derived from assisted reproductive field and has many advantages such as retrieving oocyte once with multiple transferring, increasing cumulative pregnancy rates, reducing multiple pregnancy rates and alleviating the pain due to ovarian hyperstimulation and oocyte retrieval and economic burdens. Currently, FET is mainly used in fresh cycle to prevent ovarian hyperstimulation syndrome, endometrium not suitable for transfer or fresh embryo transferred on the cycle of oocyte retrieval without pregnancy and so on. Hormone replacement FET cycle is widely applied due to monitoring simple, flexible control, low cycle cancellation rate and other advantages. Exogenous progesterone, however, is required to induce endometrial secretory transformation to receive embryo implantation and develop as hormone replacement cycle no follicular development and ovulation. Progesterone injections in inducing endometrial secretory transformation as luteal phase support is commonly used in China on account of cheap and stable pregnancy rate, but it has some disadvantages such as injection pain, abscess and panniculitis on injection site, allergic reaction, visiting hospital frequently and others ^[1]^. Sustained release vaginal progesterone gel is a micronized natural progesterone vaginal preparation, reducing local adverse reactions and having a better compliance when compared with intramuscular injection. After the first pass effect of the uterus, it spreads to cervix and corpus uteri and accumulates to a high concentration in uterus locally. Due to biological sustained release administration, progesterone concentration in the endometrium is also very stable with a lower proportion absorbed into the bloods, which effectively reduce the risk of systemic side effects ^[2]^.

It has been reported in recent years that there were no significant differences in live birth rate and clinical pregnancy rate between sustained release vaginal progesterone gel and intramuscular progesterone as luteal phase support in fresh embryo transfer cycles ^[3-6]^. And Jobanputra K, et al. performed endometrial biopsy and histologically confirmed that sustained release vaginal progesterone gel produced the same endometrial development as intramuscular progesterone in the artificial cycle ^[7]^. But, currently, there is no relevant randomized controlled trial (RCT) to compare live birth rates in hormone replacement FET with different routes of progesterone supplementation.

# 3 Objective

To compare the clinical efficacy of sustained release vaginal progesterone geland intramuscular progesterone in hormone replacement FET cycles. The primary outcome measure was live birth rate and the secondary outcome measures were clinical pregnancy, miscarriage, ectopic pregnancy and implantation rates.

# 4 Flow chart and visit

## 4.1 Flow chart

Informed consent and screening (menstruation on day 1~3):

- Medical history review
- ultrasound and physical examination

Screening failed

Hormone replacement protocol:

- Estradiol valerate 4 mg/d was administrated on day 3 of menstruation for 10 days;
- 10 days after administration, B-mode ultrasound examination was conducted. If endometrial thickness <7mm, increasing the dose of estradiol valerate to 6-8mg/d;
- If endometrial thickness was ≥7mm, progesterone would be administrated on day 0 to promote endometrium to secretory phase.

Endometrial secretory transformation on day 0

Excluded before random allocation:

Endometrial thickness <7mm

Random allocation

Group A

- Sustained release vaginal progesterone gel 90mg/d
- Dydrogesterone 20mg/d
- Estradiol valerate 4-8mg/d
- Day3 FET

Group B

- Intramuscular progesterone 40mg/d
- Dydrogesterone 20mg/d
- Estradiol valerate 4-8mg/d
- Day3 FET

Determination of pregnancy:

14 days after transfer, blood β-hCG was determined to check whether biochemical pregnancy achieved.

Pregnancy

No pregnancy

- Sustained release vaginal progesterone gel or intramuscular progesterone, dydrogesterone and estradiol valerate were withdrawn.
- Sustained release vaginal progesterone gel or intramuscular progesterone, dydrogesterone and estradiol valerate were administrated continually at the same dose.
- 5 weeks after transfer, vaginal B-mode ultrasound examination was conducted. If gestational sac and fetal heart were observed, it is defined as clinical pregnancy.
- Sustained release vaginal progesterone gel or intramuscular progesterone, dydrogesterone and estradiol valerate were withdrawn.
- 6 weeks after transfer, oral estradiol valerate was withdrawn.
- 8 weeks after transfer, sustained release vaginal progesterone gel or intramuscular progesterone was withdrawn.
- 10 weeks after transfer, dydrogesterone was withdrawn.
- Letter or telephone follow-up was performed to investigate delivery and birth outcomes.

## 4.2 Screening visit

On day 1-3 of menstruation, investigators visited patients with FET in this week, and patients had completed IVF / ICSI cycles. The detailed information had recorded. During the visit, the following items should be completed:

1. Patients signing informed consent form;
2. Reviewing medical history, such as whether there are underlying diseases and other drug use, infertility and gynecological history, and menstrual history;
3. Physical examination, including vital signs, height, weight, gynecological examination (if the examination had carried out within six months, only results were required to record);
4. Examination of the uterus and ovaries using transvaginal ultrasound;
5. Inspecting medical history to confirm whether patients satisfy exclusion criteria, including whether there are d3 frozen embryos, blood routine, hepatic and renal function, blood coagulation series, routine urine, infectious diseases, cervical smears, electrocardiogram and chest radiograph examinations.

## 4.3 Visit on the day of endometrial secretory transformation

During the visit, the following items should be completed:

1. Recording endometrial thickness, days of administration estradiol valerate and completion of the corresponding forms;
2. Excluding patients with endometrial thickness <7mm;
3. Asking patients whether any adverse events had occurred, if any, adverse event reporting form should be completed;
4. Patients randomized allocation.

## 4.4 Visit on the day of embryo transfer

The information of embryos transfer was recorded and the corresponding form was completed. Patients were asked whether any adverse events had occurred, if any, adverse event reporting form should be completed.

## 4.5 Visit on the day of determination of biochemical pregnancy

14 days after embryos transfer, blood β-hCG was determined to inspect whether biochemical pregnancy achieved and the corresponding form was completed. Patients were asked whether any adverse events had occurred, if any, adverse event reporting form should be completed.

## 4.6 Visit on the day of evaluation of clinical pregnancy

5 weeks after transfer, vaginal B-mode ultrasound examination was conducted in blood β-hCG positive patients. If gestational sac and fetal heart were observed, it is defined as clinical pregnancy. Patients were asked whether any adverse events had occurred, if any, adverse event reporting form should be completed.

## 4.7 Visit of delivery outcomes

2 weeks after expected date of confinement, telephone follow-up was performed to ask gestational age, mode of delivery, neonatal quantity, weight, with or without birth defects, and the corresponding form was completed. Patients were asked whether any adverse events had occurred, if any, adverse event reporting form should be completed.

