# 10 Duration

From September 1^st^, 2010 to January 31^st^, 2013, patients who received hormone replacement FET cycles at Reproductive Medicine Center of Renji Hospital and satisfied inclusion criteria were enrolled in the study. 10 months after transfer, patients were followed-up to investigate birth outcomes. From enrollment to follow-up completed, it would take 28 months (from September 1^st^, 2010 to December 31^st^, 2013).

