## 12.2 Definition of adverse event

Adverse event refers to the subjects participating in the study suffered any unexpected or adverse medical events, whether or not related to the study intervention. Adverse events may be any of the following:

- Signs or symptoms, including side effects of drugs;
- Abnormal laboratory parameters;
- Changes in vital signs, physical examination or test results;
- Frequency or extent (deterioration) of previous symptoms or diseases before recruitment increasing during the study.

Adverse events in this study do not include:

- Previous symptoms or diseases before recruitment without worsen during the study;
- Normal reactions related to pregnancy

Serious adverse events include any of the following occurred during the study:

- Death
- Life-threatening (there is a risk of immediate death)
- Severe or permanent disability
- Hospitalization required or prolonged
- Neonatal death at 6 weeks postpartum
- Newborns with severe congenital anomaly or birth defect
- Investigator regarding the events as serious events

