## 12.5 Immediate action following a serious adverse events

During the period of informed consent form signed to all subjects completing the trial (the end of last follow-up), if any serious adverse events occurred, investigators should fill "serious adverse event reporting form" immediately, call and send fax or e-mail to relevant safety monitor person within 24 hours. Contacts as follows:

[contact]

[contact]

E-mail: [contact]

Unless the subjects were lost to follow up, investigators should monitor and follow up all serious adverse events found in the study to symptoms stabilize or final results of adverse events clarity. Meanwhile, investigator should provide the necessary treatment and follow-up. Any new events (or follow-up information) occurred in the previous reported serious adverse events, its reporting methods and deadlines are the same as initial report.

Investigators should report adverse reactions to the Shanghai Adverse Drug Reaction Monitoring Center according to the requirements of *Management measures on adverse drug reaction reporting and monitoring*.

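### No scheduled contact is tied to the 6-week neonatal-death window in section 12.2: section 4.7 calls at due date + 2 weeks, section 10 at 10 months after transfer

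*Combined protocol and SAP*

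**What the plan says.** All references are to the combined protocol and SAP.

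- **Section 12.2** includes "Neonatal death at 6 weeks postpartum" in its list of serious adverse events. I read this as death up to 6 weeks after birth.
- **Section 12.5** runs serious-adverse-event reporting from consent to "all subjects completing the trial (the end of last follow-up".
- **Section 4.7**, the last visit in section 4, states: "2 weeks after expected date of confinement, telephone follow-up was performed". The purpose of the call is "to ask gestational age, mode of delivery, neonatal quantity, weight, with or without birth defects". It also carries the general safety question: "Patients were asked whether any adverse events had occurred, if any, adverse event reporting form should be completed".
- **Section 10** states: "10 months after transfer, patients were followed-up to investigate birth outcomes". It adds: "From enrollment to follow-up completed, it would take 28 months", and prints 1 September 2010 to 31 December 2013 beside that figure.
- **Sections 4.1 and 5.5** mention follow-up of delivery and birth outcomes by letter or telephone but give no time for it.
- **CRF page 10** (the delivery form) records the numbers of live births and stillbirths and, for each newborn, sex, weight and birth defects. It has no item on whether a live-born infant survived.

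**The concern.** The plan names a serious outcome with a 6-week horizon, but its visit schedule ends with a call set by the due date, not by the delivery. For an infant born near term that call comes well before 6 weeks. The other follow-up time, in section 10, is about four weeks later, and nothing says which of the two governs.

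The form adds to the problem. Section 12.2 lists two newborn outcomes. Birth defects have a question in section 4.7 and a box on the delivery form. Neonatal death has neither, so even a death before the call would come to light only through the general adverse-event question.

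What is at stake is complete ascertainment of neonatal deaths in both arms. Treatment is open (section 5.2), so a count that leans on spontaneous reports is weaker than one based on the same question put to every woman at the same time.

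**Working it through.** **Inputs.** From the documents: call at due date + 2 weeks (4.7); follow-up 10 months after transfer (10); 6-week window, or 42 days (12.2); day-3 embryos (6); enrolment 1 September 2010 to 31 January 2013 (6 and 10); end date 31 December 2013 (10). Assumed, because the documents do not give them: the due date falls at 40 weeks of gestation, and due date = transfer + 263 days (266 days from fertilisation less 3 for a day-3 embryo).

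**Step 1: the printed duration.** The plan's figure does not reproduce. 1 September 2010 to 31 December 2013 is 40 months, not 28. Enrolment alone is 29 months. Twenty-eight months from the start would end on 31 December 2012, before enrolment closes.

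**Step 2: the two follow-up times.**
- Section 4.7: 263 + 14 = day 277 after transfer, and 277 / 30.4375 = 9.1 months.
- Section 10: 10 × 30.4375 = about day 304.
- Difference: 304 − 277 = 27 days.

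**Step 3: infant age at each contact.** For a birth at G weeks:
- age at the 4.7 call = (40 − G) + 2 = 42 − G weeks, which does not need the 263-day assumption;
- age at 10 months = (304 − 263) + 7 × (40 − G) = 41 + 7 × (40 − G) days;
- uncovered days = 42 minus the age in days, or 0 if that is negative.

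| Birth (weeks) | Age at 4.7 call (days) | Uncovered of 42 | Age at 10 months (days) | Uncovered of 42 |
|---|---|---|---|---|
| 36 | 42 | 0 | 69 | 0 |
| 37 | 35 | 7 | 62 | 0 |
| 38 | 28 | 14 | 55 | 0 |
| 39 | 21 | 21 | 48 | 0 |
| 40 | 14 | 28 | 41 | 1 |
| 41 | 7 | 35 | 34 | 8 |
| 42 | 0 | 42 | 27 | 15 |

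The 4.7 call reaches 6 weeks only for births at or before 36 weeks. The 10-month contact reaches it for births up to about the due date.

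**Step 4: sensitivity to the 263 days.** Moving the interval 3 days either way gives an age at 10 months, for a due-date birth, of 304 − 260 = 44 days or 304 − 266 = 38 days. For a birth at 41 weeks the ages are 37 and 31 days, both short of 42. The conclusion for later births does not change.

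**Step 5: would a later contact fit the end date?** A call at due date + 8 weeks gives an infant age of 48 − G weeks, which is 6 weeks at G = 42. I assume transfer 3 days after secretory transformation.
- If 31 January 2013 is the last randomisation: transfer 3 February, due date 24 October, call 19 December 2013.
- If 31 January 2013 is the last consent, on menstrual day 1: estradiol from 2 February for 10 days, transformation 12 February, transfer 15 February, due date 5 November, call 31 December 2013. Longer estradiol preparation under section 5.3 would push this into January 2014.

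**The case against.** A reader might infer that neonatal deaths cannot be observed for most infants, because safety collection stops at the 4.7 call. The documents do not support that.

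- Section 12.5 can be read as a reporting period that ends for the trial as a whole, not for each woman at her own call. Section 12.3 requires adverse events reported by subjects to be recorded. A death after the call could therefore still enter the record.
- Neither the 4.7 call nor the section 10 follow-up is labelled as the last contact. If the section 10 time governs, or both contacts take place, the shortfall is small for a due-date birth and lies mainly in later births.
- A reader might also infer that about two thirds of the window is lost for any term birth. That share (28 of 42 days) holds only for birth on the due date and only under section 4.7; the table runs from 7 days at 37 weeks to 42 days at 42 weeks. The documents give no distribution of gestational age, so the proportion of infants affected cannot be stated.
- The plan mentions separate adverse-event and serious-adverse-event forms, which could hold a neonatal death. They are not in the text available, so their content cannot be judged.
- Neonatal death is not among the outcomes in sections 5.6 and 9, and the sample size is untouched.

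These points stand, and they limit the finding. They do not supply a scheduled enquiry: a separate form is completed only once someone learns of the death. Reading 10 months as lunar months (280 days) would nearly reconcile the two times, leaving 280 − 277 = 3 days, but nothing in the text suggests that reading, and a due-date infant would then be only 280 − 263 = 17 days old.

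**Conclusion.** The point holds as a gap in systematic ascertainment and an inconsistency between sections. Under section 4.7, every birth after 36 weeks lacks a scheduled enquiry over the full 6 weeks, by 4 weeks for a birth on the due date. Under section 10, read in calendar months, the gap is about 1 day for a due-date birth, 8 days at 41 weeks and 15 days at 42 weeks. The section 10 figures rest on the assumed 263-day interval; those for section 4.7 need only a due date at 40 weeks.

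The number of deaths that would be missed cannot be derived from the documents. The live-birth primary endpoint is little affected, since both contacts fall after the due date. The 28-month figure is a clerical slip: the printed dates are consistent with the follow-up, so the error lies in the number and not in the dates.

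**What to change.** 1. State one final contact, in the same words, in section 4.7 and section 10, timed to reach 6 weeks after delivery. Due date + 8 weeks is one workable choice: it covers births up to 42 weeks and does not require the delivery date to be known in advance.
2. Add to CRF page 10, for each infant: alive at 6 weeks, yes or no, and date of death if no. Add infant survival to the items asked in section 4.7.
3. Say in section 12.5 whether the reporting period ends with each woman's final contact or with the last contact in the trial.
4. Correct 28 months to 40 months in section 10.

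**Cost.** No additional contact is needed if the existing call is moved. It would be 6 weeks later than section 4.7 now has it, or 4 weeks later for a due-date birth if the call is timed at 6 weeks after actual delivery. Against the 10-month time in section 10, due date + 8 weeks (day 263 + 56 = 319) is about 15 days later. The form gains one item per infant. The last call falls about 19 December 2013 if 31 January 2013 is the last randomisation date, and on 31 December 2013 or slightly later if it is the last consent date. The plan should say which of these it means and, in the second case, allow a short margin on the end date.

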# 9 Outcome measures

The primary outcome measure was live birth rate and the secondary outcome measures were included clinical pregnancy, miscarriage, ectopic pregnancy and implantation rates.

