**Inspection Visit Form for the Date of Clinical Pregnancy Assessment**

**(Page 9)**

1. This B –scan shall be conducted within ___days after the embryo transfer.
2. Whether or not the patient has obtained the clinical pregnancy?

□Yes

The number of intrauterine gestational sac：

The number of embryos with fetal heart beat：

□If no，the results shall be：

□Biochemical pregnancy miscarriage

□Right fallopian tube pregnancy

□Left fallopian tube pregnancy

□CHM

□PHM

□Heterotopic pregnancy

3. EDC of the patient：__ ____ __/__ __/__ __ （Y/M/D）

Research Program：A comparison of live birth rates between sustained release vaginal progesterone gel and intramuscular injection of progesterone in hormone replacement frozen-thawed embryo transfer cycles:

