**Inspection Visit Form for Condition of Delivery** **(page 10)**

1. Date of Delivery：__ ____ __/__ __/__ __

2. Gestational age at the childbirth：Pregnant for __ __ Week

3. Vaginal delivery？□Yes □ No

4. Cesarean section？□Yes □ No

5. Number of live births：

6. Stillbirth？ □Yes □ No

Number of stillbirth：

Reasons for stillbirth？（Tick ​​all that apply）□Unspecified

□Birth Defects

□Placental abnormality

□Fetal Growth Retardation

□Infection

□Mother’s disease

□Umbilical cord accident

□Others（Please specify）：_________________

7. Newborn 1 Information

1）. Neonatal sex：□Male □Female

2）. Neonatal birth weight： __ __ __ __ g；

3）. Existence of birth defects：□Yes □ No

8. Newborn 2 Information

1）. Neonatal sex：□Male □Female

2）. Neonatal birth weight： __ __ __ __ g；

3）. Existence of birth defects：□Yes □ No

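### After the 5-week scan no item on the forms shown records clinical miscarriage, termination or a woman not reached, so the miscarriage rate has no direct source and some unknown live-birth outcomes cannot be identified

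*Combined protocol and SAP*

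**What the plan says.** Section 9 states "The primary outcome measure was live birth rate" and then "the secondary outcome measures were included clinical pregnancy, miscarriage, ectopic pregnancy and implantation rates". Sections 3 and 5.6 also name miscarriage. No section defines it or gives its denominator.

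The outcome data come from these places:

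- **Transfer form (CRF page 7)** records why a transfer was not done.
- **Pregnancy test form (page 8)** records biochemical pregnancy, yes or no.
- **5-week scan form (page 9)** records clinical pregnancy. A yes is followed by counts of intrauterine sacs and of embryos with a heartbeat. A no is followed by a list: "Biochemical pregnancy miscarriage", tubal pregnancy on either side, complete or partial mole, and heterotopic pregnancy.
- **Delivery call (section 4.7)**, two weeks after the due date: "telephone follow-up was performed to ask gestational age, mode of delivery, neonatal quantity, weight, with or without birth defects". The section adds: "Patients were asked whether any adverse events had occurred, if any, adverse event reporting form should be completed".
- **Delivery form (page 10)** records delivery date, gestational age at childbirth, mode of delivery, "Number of live births", stillbirth yes or no with "Number of stillbirth" and reasons, and newborn details.

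Section 11.1 allows for about 10% dropout without defining it. Section 11.2 refers to what appears to be an intention-to-treat analysis and gives no rule for an unknown live-birth status. Loss to follow-up is mentioned only in section 12.5, for serious adverse events.

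**The concern.** Between the 5-week scan and the call after the due date, a pregnancy can end in miscarriage or termination, or the woman can become unreachable. None of these has its own item in the call or on page 10. If page 10 is left blank, the analyst knows only that there was a clinical pregnancy and that no birth was recorded.

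Two results are exposed. The miscarriage rate would have to be found by subtraction, which counts women lost to follow-up as miscarriages. For the primary outcome, the women concerned are those with a clinical pregnancy, the group from which the live births come. Their missing outcomes could not be separated from true losses or compared between arms. Section 5.2 says that investigators and patients both know the allocation, so a comparison of missing outcomes by arm is worth having. Information not collected at this one late call may be hard to recover afterwards.

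**Working it through.** **1. What the forms can and cannot separate**

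| Outcome | Recorded where |
|---|---|
| No transfer | Page 7, with reason |
| Negative hCG | Page 8 |
| Biochemical loss, tubal or molar pregnancy | Page 9 |
| Sac without fetal heart at 5 weeks | No option in the page 9 no list; visible from the counts only if clinical pregnancy is ticked yes |
| Miscarriage or termination after the scan | No item |
| Stillbirth, live birth | Page 10 |
| Not reached | No item |

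The fourth row depends on the definition used. Sections 4.1 and 4.6 require a sac and a fetal heart for clinical pregnancy, so a sac alone is a no, and no listed option fits it. Section 5.5 requires only a sac, so the same woman is a yes.

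**2. The plan's own figures**

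With 40% against 30%, two-sided alpha 0.01 (sidedness is not stated; two-sided is assumed) and 90% power:

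n = [2.576 × √(2 × 0.35 × 0.65) + 1.282 × √(0.40 × 0.60 + 0.30 × 0.70)]² / 0.10² = 675 per group.

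Then 675 / 0.90 = 750 per group. Both figures reproduce, and nothing in this point changes them.

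**3. Miscarriage by subtraction (illustration)**

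Let L be the fraction of clinical pregnancies lost to follow-up after the scan and m the true miscarriage rate, with loss unrelated to outcome. Ignore terminations and stillbirths. Subtraction reports L + (1 − L)m, an excess of L(1 − m). Neither L nor m is in the documents. The plan's 10% dropout applies to all randomised cycles, not specifically to women after the scan.

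| L | m = 15% | m = 20% |
|---|---|---|
| 5% | 0.05 + 0.95 × 0.15 = 19.25% | 0.05 + 0.95 × 0.20 = 24% |
| 10% | 0.10 + 0.90 × 0.15 = 23.5% | 0.10 + 0.90 × 0.20 = 28% |
| 15% | 0.15 + 0.85 × 0.15 = 27.75% | 0.15 + 0.85 × 0.20 = 32% |

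At L = 10%, losses to follow-up make up 0.10 / 0.235 = 43% to 0.10 / 0.28 = 36% of the women without a birth record.

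I give rates and not counts because the plan's inputs disagree on the number of pregnancies. The two domestic clinical pregnancy rates in section 11.1 (23.5% and 34.8%) give 352 to 522 pregnancies in 1500 women. The design rates give 0.40 × 750 + 0.30 × 750 = 525 live births, which is more than either.

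**4. Primary outcome (illustration)**

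Suppose 10% of live-birth outcomes are unknown in each arm, unrelated to outcome, and are scored as no live birth. The rates become 0.40 × 0.90 = 36% and 0.30 × 0.90 = 27%, a difference of 9 points. Power with 750 per group is 88.1%. Leaving the unknowns out (675 per group) gives 90.0%.

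Bias under the null needs unequal loss. With a true rate of 35% in both arms and assumed losses of 5% and 15%, the same scoring gives 0.35 × 0.95 = 33.25% and 0.35 × 0.85 = 29.75%. That is a spurious difference of 3.5 points, in either direction.

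**The case against.** A reader might infer that the miscarriage rate cannot be computed at all. The documents do not support that. Biochemical loss has its own box. Where clinical pregnancy is ticked yes, the page 9 counts show a sac without a heartbeat. Section 4.7 says the form is completed at the call, so a woman who is reached after a miscarriage can be entered with 0 live births and no stillbirth, which differs from a blank page. The call also asks about adverse events, and section 12.2 makes hospital admission a serious adverse event. The adverse event forms are mentioned but are not in the text available, so absence from the whole CRF is not proven.

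These points stand, but they leave the gap open. Nothing tells staff to enter 0, and 0 with no stillbirth does not separate miscarriage from termination. Section 12.2 excludes normal reactions related to pregnancy without saying where miscarriage falls. A question put to the patient cannot record that she was not reached.

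A reader might also infer that every missing primary outcome looks like a failure, or that the plan scores a blank as no live birth. Neither follows. Earlier failures and stillbirths are recorded, and section 11.2 states no scoring rule. Nor do the documents give any evidence that loss would differ between arms.

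**Conclusion.** The point holds in limited form. After the 5-week scan, clinical miscarriage, termination and not reached have no item in the call or on page 10, and page 9 has no option for an intrauterine sac without a fetal heart. The miscarriage rate cannot be derived directly or reliably from the forms shown. The ambiguity over live birth is confined to women with a clinical pregnancy and a blank page 10, and the plan does not say how an unknown status is handled.

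The size depends on assumptions. At 10% loss after the scan, subtraction overstates a 15-20% miscarriage rate by 8 to 8.5 points. Equal 10% loss scored as failure costs the primary comparison about 2 points of power, and a spurious difference arises only if loss is unequal. This is a should-fix: it removes the direct source for a named secondary outcome and obscures missing data in the primary one, but the figures do not show that the primary comparison fails.

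**What to change.** 1. Add one mandatory item to CRF page 10 and to the section 4.7 call: pregnancy outcome, with the options live birth, stillbirth, miscarriage (date and gestational week), termination, ectopic, and not reached (date of last contact).
2. Reconcile the definitions of clinical pregnancy in sections 4.1 and 4.6 with that in section 5.5, then add intrauterine sac without fetal heart to page 9 accordingly.
3. Define miscarriage and its denominator in section 9, and compute the rate only from the recorded outcome.
4. In section 11.2, state how an unknown live-birth status is handled, report unknowns by arm, and add a sensitivity analysis of live birth for them.

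The cost is one extra item at a call already planned, a revised option list on page 9, a few sentences in the protocol and a little more analysis. The sample size stays at 750 per group.
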